# Family Club Denmark #strongertogether - a volunteer intervention for disadvantaged families: study protocol for a quasi-experimental trial

**DOI:** 10.1186/s40359-020-00426-0

**Published:** 2020-06-01

**Keywords:** Volunteer, Third sector, Parenting, Family, Support, Intervention, Effectiveness

## Abstract

**Background:**

Need-oriented family support programs are examples of voluntary-based interventions increasingly recognized by the public sector as an important contribution to health and social care provision. Voluntary interventions are attractive because of their focus on activism, inclusion, and participation, but also their low cost and easy accessibility. There is an increasing demand for documentation of the effectiveness of family support programs. Methodologically sound studies are, however, limited and findings are generally inconsistent. This trial aims to assess the effectiveness of the volunteer-based intervention Family Club Denmark on parental stress, mental health, development and well-being of parents and children and to get insight into the experiences of both volunteers and families.

**Methods:**

This is a prospective quasi-experimental trial with two conditions: (1) intervention group participating in Family Club Denmark and (2) wait-list control group. Participants are families with children aged 2–12 years who wish to participate in the program. Participants are allocated to intervention primarily after a first-come-first-serve principle, and further families will join the wait-list and be offered participation after around 6 months. Quantitative data are collected through web surveys at three time-points: at baseline, post-intervention (6 months after baseline), and follow-up (12 months after baseline). The primary outcome is mental health. Secondary outcomes include parenting behavior, parenting stress, self-efficacy and self-worth, family routines and child well-being. Qualitative data are collected through observations, focus groups, and interviews.

**Discussion:**

This trial is among the first experimental studies of a group-based third sector need-oriented family support program offered to a wide array of families. The trial will provide important knowledge on the effectiveness of a volunteer-based family intervention on important outcomes such as mental health, self-efficacy, family routines. Furthermore, the trial will provide knowledge on volunteer, parent, and child experiences with participating in the intervention and knowledge on how to conduct experimental trails in a complex volunteer environment.

**Trial registration:**

ClinicalTrials.govNCT03657888 (registered 29.08.2018).

## Background

Civil society is gaining increased attention and recognition as a significant partner in the welfare state. Membership in democratic associations is considered a core element of Nordic welfare and has ensured democratic influence in the community and society as a whole. There is a large degree of cooperation between the state and civil society organizations, and voluntary organizations serve as intermediate institutions between the citizens and the state [1]. In Denmark, associations with member volunteers dominate the tradition and there is a high degree of participation measured per resident in democratic organizational models in local, regional and national formats [1–3]. Voluntary activities arising from civil society are often referred to as ‘the third sector’, as it is delimited from both the private and the public sector. These activities are – due to their innovative solutions to problems and their democratic structures - increasingly regarded as important contributions to solving complex problems such as loneliness, social problems and health problems [4–7]. In Denmark, for instance, civic engagement in health and social care has received awareness and recognition from the Danish Health Authority and the National Board of Social Services) [8–11] for their valuable contribution. The public sector finds the opportunity of drawing on voluntary efforts in the delivery of welfare services appealing because it offers a (partial) solution to scarce public resources and has the potential to cater to new needs and demands in society [4–6]. Hence, voluntary services are intuitively considered valuable; especially in cases where costly professional work is shifted towards non-professional, inexpensive support.

Civil society organizations work with a wide range of different purposes and characteristics, including development from collective to individual engagement, from member-based to program-based efforts, and from institutionalized to self-organized activities. Activities that all coexist with the traditional association- and membership-based civil society organizations [12]. The nature of voluntary activities has evolved during recent decades and volunteerism has recently been subject to increased marketization involving increased demand for and focus on performance, impact, and documentation [13]. This focus can potentially conflict with the democratic and inclusive nature of the civil society [14–16]. Existing literature on the impact of voluntary interventions within the health and social care represents different approaches and methodologies. However, methodologically sound studies such as randomized controlled trials (RCTs) and well-designed cohort studies are limited [17]. Without such evidence, no firm conclusions can be drawn about the impact of volunteer interventions [17]. The current literature covers a broad spectrum of interventions [7, 18–36] ranging from elderly and end-of-life voluntary care [6, 37, 38], voluntary care for left-behind children [22], programs targeting struggling readers [24], prevention and early detection of cancer [39] to need-oriented family support programs [25–28, 32, 33, 40].

The current study represents the latter. The intervention examined in this study is Family Club Denmark (FCD). FCD is a voluntary program targeting vulnerable families by creating communities between families with different social backgrounds supported by one voluntary leader and two-to-five further volunteers. FCD is a family support program aiming to increase the network for both children and parents in vulnerable families and promote positive parenting such as behavior, competence, development and family functioning.

The literature on the effectiveness of volunteer family support programs finds mixed results due to differences in programs (e.g targets and timing), expected outcomes and research design. Kelleher & Johnson evaluated the Cottage Community Care Pilot Project using a descriptive comparative design and concluded that the intervention group experienced greater improvements in seven aspects of family functioning compared to the control group. However, the improvements were only statistically significant for two aspects [25]. Caring in Chaos (CiC) is a parenting intervention targeting families of children with parental concerns about ADHD. In an RCT the intervention group comprising 80 families receiving CiC was compared to a wait-list condition. The trial suggested improved parental behavior, sense of competence, parental stress and depressive symptoms as well as child function at post-treatment. At 4 month’s follow-up, most of these effects were sustained [40]. Gardner et al. carried out an RCT examining the effectiveness of a parenting intervention for reducing child conduct problems.0 76 children aged 2–9 years were randomized to either receiving a video-based 14-week program or to a wait-list control. Comparing the two groups after 18 months indicated significant improvements in outcomes such as observed child negative behavior, child independent play and parents’ sense of competence as well as observed and self-reported positive parenting but with no change in maternal depression [41]. Another example of a family support program is Home-Start which was initiated in the UK in 1973 but has now spread to 22 countries [42]. Home-Start offers volunteer support to vulnerable families with at least one child below 5 years of age [43]. Gentry et al. examined the effectiveness of Home-Start Suffolk (UK) using a mixed-methods design and concluded that stakeholders perceived the program as successfully supporting families in need of additional help. However, poor quality of administrative data hampered a quantitative analysis of effectiveness [4]. Other evaluations of the Home-Start initiative include quasi-experimental studies and uncontrolled studies that have found somewhat mixed results. In a quasi-experimental study, Asscher et al. found positive effects of Home-Start on maternal competence, mixed effects on parenting behavior and no effects on maternal depressive moods and child behavior at the end of the intervention (approx. Six months) [44]. Results were based on self-reported and observational data. Two additional quasi-experimental studies with longer follow-up showed the greatest improvement in parental well-being, behavior, and competence during the intervention, and these changes were sustained until 10 years after the intervention [26, 45]. Barnes et al. evaluated the impact of Home-Start on maternal depression after labor in an uncontrolled randomized study, and found no reduction in the risk of depression among new mothers [27]. This finding is supported by a quasi-experimental study that demonstrated perceived improvements in maternal well-being but failed to demonstrate statistically significant effects on several indicators of maternal well-being including parental stress, maternal depression and maternal self-esteem between the groups compared [43]. In addition to providing inconsistent results, the literature is challenged by shortcomings such as high and potentially selective attrition rates [26, 45], small sample sizes [25–27, 41, 44–46], lack of randomization [26, 44–46], no comparison group [4] and no complete blinding of the observer [44].

Generally, methodologically sound studies on the impact of volunteer family support programs are limited, and findings are generally inconsistent due to differences in study methodologies, outcomes examined and characteristics of the programs investigated. Results of meta-analyses and systematic reviews support this by showing varying effect sizes and directions of effects depending on included studies and outcomes of interest [47–49]. Despite inconsistent results, family support programs carried out by volunteers are still continuously being developed and implemented. However, there is a need for ongoing systematic and rigorous evaluations to document the effectiveness of these interventions. The current study is a prospective quasi-experimental trial contributing to this evidence-base. The trial aims to assess the effectiveness of the volunteer intervention Family Club Denmark (FCD) on parent stress, mental health, development, and well-being of parents and children. We will also examine the implementation of FCD concept across organizations, the experience of volunteering within FCD, and the experiences of the participants. The hypothesis is that families in the FCD group will improve more than the control group on all outcomes.

## Methods and design

The study is a prospective quasi-experimental trial with two conditions: (1) intervention group participating in Family Club Denmark and (2) wait-list control group. The trial aims to examine the effectiveness of Family Club Denmark. The primary outcome of the study is mental well-being and secondary outcomes comprise parenting behavior, parenting stress, self-efficacy and self-worth, family routines, and child well-being. Participants will be allocated to the intervention group primarily after a first-come-first-serve principle. When the maximum number of participants in a specific family club is reached, any further families will join the wait-list and be offered participation after 6 months if a family club exists in the area they live in. The control group will also include families who sign up for a family club in an area where a family club does not yet exist. The study takes place in all five different regions of Denmark. Recruitment commenced in September 2018 and is planned to close in early 2020. We will recruit participants from family clubs starting in fall 2018, spring and fall 2019, and spring 2020. The FCD project is a collaboration between the three third sector partner organizations; KFUMs Sociale Arbejde, FDF, and KFUM Spejderne.

Participants will receive written information on the project and will give electronic written consent to participate in the trial. Ethical approval has been obtained from the internal review board at VIVE. According to Danish law, the project does not need to obtain approval from The Danish National Committee on Health Research Ethics. The protocol conforms to the Standard Protocol Items: Recommendations for Interventional Trials (SPIRIT) guidelines (Fig. 1). The final reports of the trial will be written following the Consolidated Standards of Reporting Trials (CONSORT) statement.

**Fig. 1 Fig1:**
[figure not shown]
Schedule of enrolment, interventions, and assessments

### Participants

Participants are vulnerable and non-vulnerable families with children aged 2–12 years who wish to participate in FCD. Most vulnerable families will be characterized by at least one of the following characteristics: being a single parent, having low income, having a small or no network, experiencing a low level of support, experiencing loneliness or lack of contact with other adults, having difficulty creating relationships, having physical or mental health problems, or having a hard time making ends meet during the week. To be included in the trial families must have at least one child 2–12 years old and sign up for FCD. Families are excluded if they are not able to fill out questionnaires in Danish. The vulnerability classification of families is based on labor market status, and the motivation for participation in FCD stated at sign up. Families are classified as vulnerable if at least one parent is outside the labor force (for reasons other than enrollment in education) or unemployed and/or the motivation for participation in at least one of following: Our daily life is very stressful, we feel lonely, we have many conflicts in our daily life, we struggle as a family, we find it hard to become part of new social networks.

### Recruitment

We aim to recruit 200 vulnerable families – 80 to wait-list and 120 to FCD. Participants are recruited through the FCD website, by Facebook adds, by municipal social workers, by local social housing employees, and by direct contact with the local FCD volunteers. The three partner organizations have employed project coordinators to find venues, recruit volunteers, recruit families, handle the website and sign-up, and support volunteers. In most cases, the recruitment process is as follows: (1) A family applies for a specific family club through the website and gives consent for VIVE to contact the family; (2) A project coordinator creates a list with participants; (3) The project coordinator allocates participants to intervention or wait-list control; (4) The project coordinator sends contact information and allocation condition to VIVE; (5) The project coordinator informs VIVE about the starting dates of the family clubs; (6) VIVE sends the first questionnaire (including electronic consent to participate) by text-message and e-mail; and (6) The project coordinator informs participants about allocation. Most families are recruited through the FCD website but some are recruited directly at the local site e.g. through an existing scout unit or the local social housing office. In some cases, families will sign up after the FCD has started.

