### Allocation

Families are allocated to a family club or a waitlist based on a first-come-first-serve principle conditional on their vulnerability classification. Around nine families are allocated to one family club and any extra families will be offered to be on a wait-list for the next round or when another club starts in the area at a later timepoint. The coordinators strive to allocate two or three non-vulnerable families to each family group to make sure that non-vulnerable families are present in all clubs. The coordinators also make sure that families with sufficient Danish language skills are present in each club making it possible for families that do not have Danish as their first language to improve their Danish skills. The discretionary allocation of families, carried out by the coordinators, is made without further regards to family characteristics and thus can be considered as good as random conditional on vulnerability status and Danish language skills. Families that sign up for FCD but live in an area where there is currently no FCD are included in the wait-list control group. Families who have been assigned to FCD are included in the wait-list control group if the start of the FCD is delayed by at least 4 months. Families who have been assigned to FCD but are not able to participate, e.g. because they have other obligations on the assigned day, and families who do not show up for FCD are included in the wait-list control group. The flowchart is presented in Fig. 2.

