**Fig.2 Fig2:**
[figure not shown]
Study flow chart

The first-come-first-served principle potentially introduces selection issues if first responders differ from later attendees by e.g. being more enthusiastic. The recruitment strategy, involving the use of several channels that target potential families in very different approaches, can to some extent mitigate the selective timing of sign up. The mix of personal recruitment by municipal social workers or local social housing employees with the online recruitment process can introduce some randomness in who signs up when. Also, first responders can be assigned to the control group for other reasons such as no club in their local area, or the family could not participate on the day that the club was offered. We expect that most families are allocated to the control group because they sign up for an FCD in an area where there is not yet any FCD. Therefore, we expect that the potential selection issues introduced by the first-come-first-served principle are minimized.

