### Statistical analysis

We analyze the primary and secondary outcomes at post-intervention (T2) and follow-up (T3). We use linear regression for normally distributed outcomes and apply robust standard errors to correct for the correlation between observations participating in the same FCD group. In the case of heavily skewed data, we use non-parametric rank-based tests. To check whether the first-come-first-served principle or the allocation of vulnerable families conducted by the volunteers introduce imbalances in the allocation to FCD and the waitlist control, we test for statistical differences in observable characteristics of the two groups using t-tests. In the analysis of the effectiveness of FCD, the hypothesis tested for each outcome is that the FCD group will score better than the wait-list control group. We test this hypothesis with a binary variable indicating the intervention group. We include variables measured at baseline with indications of imbalances (*p* < 0.1) as control variables and apply two-sided tests with 0.05 significance levels throughout. As all outcomes represent a different aspect of the expected outcome of the intervention we do not consider multiple testing issues. We analyze primary and secondary endpoints according to an intention-to-treat (ITT) principle and handle missing data with multiple imputations. Parametric imputation models are preferred, but in case of severe non-normality or convergence issues, we use predictive mean matching or other non-parametric options. We include the 12-month outcome data for exploratory analyses but can also be used as tools in secondary analyses of missingness. Exploratory analysis of data from all three measurements (T1 - baseline, T2 - 6 months and T3–12 months) will be carried out using mixed-effect regression and possibly latent growth curve analysis. The purpose is to assess the longer-term effects of the intervention and to understand how the psychosocial characteristics of the families involved develop over time. In addition to the primary analysis, we will perform subgroup analyses to examine potential differences between subsets of participants. Hence, we analyze subgroups according to the following characteristics: vulnerability (vulnerable or non-vulnerable families); family composition (single parents or cohabiting parents); the age of target child (< 8 years old or ≥ 8 years old); partner organization (KFUMs Sociale Arbejde, FDF, or KFUM Spejderne); the number of volunteers in the FCD; and the number of sessions attended (dose).

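### Intake wave is not a prespecified factor, although non-random allocation over four waves may tie arm to calendar time and season

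*Protocol article*

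**What the plan says.** **Intake.** Methods and design: "We will recruit participants from family clubs starting in fall 2018, spring and fall 2019, and spring 2020".

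**How arm is set.** Allocation describes first-come-first-serve places, conditional on vulnerability status. Families beyond a club's capacity go to the wait-list. So do families whose club is delayed by at least 4 months, and families who cannot attend or do not show up. It adds: "Families that sign up for FCD but live in an area where there is currently no FCD are included in the wait-list control group". The text after the flow chart expects this to be the main source of controls: "most families are allocated to the control group because they sign up for an FCD in an area where there is not yet any FCD".

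**Survey timing.** Recruitment opens with "In most cases, the recruitment process is as follows" and lists, as consecutive steps, "The project coordinator informs VIVE about the starting dates of the family clubs; (6) VIVE sends the first questionnaire". It also notes: "In some cases, families will sign up after the FCD has started". Outcomes sets T2 and T3 at 6 and 12 months after baseline in both arms.

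**Model.** Statistical analysis: "We test this hypothesis with a binary variable indicating the intervention group". Covariates are those baseline variables that show imbalance at p < 0.1. Tests are two-sided at 0.05. Intake wave, season and calendar time are not named as covariates, balance checks or subgroups.

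**The concern.** In a randomised trial, season and calendar time would be balanced by design. Here nothing guarantees that. Whether a family becomes an FCD family or a control depends on when it signed up, whether its area had a club by then, and whether that club started on time. All three are linked to the roll-out, so the mix of waves may differ between arms.

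T2 and T3 are counted from T1, so any difference in T1 calendar time carries into both. If well-being varies by season or over the 18 months or so of intake, the arm coefficient absorbs part of that variation unless wave is in the model. The stated rule leaves its inclusion to a significance screen on a variable that the plan does not name.

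**Working it through.** **1. The plan's own power figure.** Inputs from Power considerations: 120 FCD, 80 control, SMD 0.35, baseline correlation 0.50, two-sided 0.05.
- Baseline-adjusted SD = sqrt(1 - 0.50²) = 0.866.
- SE = 0.866 × sqrt(1/120 + 1/80) = 0.125 SD.
- Power = Φ(0.35/0.125 - 1.96) = Φ(0.84) = 0.80, which reproduces the stated approx. 80%.
- Without baseline adjustment the SE is sqrt(1/120 + 1/80) = 0.144 and power is 0.68. The plan's figure therefore presumes baseline adjustment.

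**2. Would the p < 0.1 screen find a wave imbalance?** Take one fall/spring indicator with shares 0.5 ± d/2 in the two arms. Selection probability = Φ((d - 1.645 × SE0)/SE1), where SE0 is the pooled and SE1 the unpooled standard error of the difference. For d = 0.10, SE0 = 0.0722 and SE1 = 0.0718, so Φ(-0.26) = 0.40.

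| Difference in mix, d | Probability selected |
|---|---|
| 10 points | 0.40 |
| 15 points | 0.67 |
| 20 points | 0.88 |
| 30 points | >0.99 |

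**3. Size of the bias if wave is left out.** The documents give no seasonal effect and no wave mix by arm, so both are assumptions. Bias = s × d, where s is the seasonal difference at T2 in SD. Type I error = Φ(-1.96 + bias/SE) + Φ(-1.96 - bias/SE).

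| s | d | Bias (SD) | Type I error, SE 0.125 |
|---|---|---|---|
| 0.1 | 0.2 | 0.02 | 0.053 |
| 0.2 | 0.2 | 0.04 | 0.062 |
| 0.2 | 0.4 | 0.08 | 0.098 |
| 0.3 | 0.4 | 0.12 | 0.160 |

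The range of 0.02-0.12 SD is 6-34% of 0.35. With the unadjusted SE of 0.144, the type I error runs from about 5% to 13%.

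One sensitivity case is less favourable. T1 and T2 are six months apart, so they may fall in opposite seasons. Adjusting for baseline with slope 0.5 then gives s × d + 0.5 × s × d = 1.5 × s × d, or 0.03-0.18 SD over the same inputs.

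**4. Cost of adjusting for wave.** Take an illustrative, strongly unbalanced mix: 15/20/30/35% in FCD (18, 24, 36, 42 families) and 35/30/20/15% in controls (28, 24, 16, 12).
- Within-wave information = Σ n1·n0/(n1 + n0) = 10.96 + 12.00 + 11.08 + 9.33 = 43.4.
- Ignoring wave: 120 × 80/200 = 48.
- SE ratio = sqrt(48/43.4) = 1.05.
- Power = Φ(0.35/(0.125 × 1.052) - 1.96) = Φ(0.70) = 0.76.

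**The case against.** The strongest reply is that no timing difference is shown. A reader might infer that the club start date triggers T1, so that controls without a club are surveyed in other seasons. The documents do not support that. Recruitment gives an order of steps for most cases, not a trigger. Coordinators list and allocate both conditions together, and VIVE then surveys them, which fits same-batch surveying equally well. The missing T1 rule for no-club families is operational detail that an article may leave to the full protocol. This part of the reply stands.

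A reader might also infer that wave cannot enter the model because a four-level factor cannot be t-tested. That is wrong. The balance check covers observable characteristics, and wave dummies, a season indicator or T1 date can all be tested. At 20 points or more the screen would usually catch a season imbalance. Where it often fails, the bias is small: 0.01-0.03 SD at 10 points and 0.015-0.045 SD at 15 points. This limits the point but does not remove it, because the screen helps only if someone chooses to test a variable that the plan never names.

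A third tempting reading is that a longer wait between sign-up and T1 in one arm biases T2, because families sign up at a low point and recover. The documents state no such dip. Suppose it anyway: a mean of -0.5 × 0.5^(m/6) SD at m months after sign-up. A 4-month lag then shifts T1 by 0.185 and T2 by 0.093, and baseline adjustment with slope 0.50 removes 0.50 × 0.185 = 0.093, leaving nothing. Whether baseline is always in the model is a separate question.

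Finally, the Discussion already calls causal conclusions tentative. That is fair, but it does not replace adjustment for a known design variable.

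**Conclusion.** The point holds as a weakness in the prespecified model. Arm is assigned non-randomly over four waves, and the covariate rule neither names wave nor reliably detects a modest imbalance in it. The documents do not establish that T1 timing differs by arm, so the bias is a risk of unknown size. Under the stated assumptions it is about 0.02-0.12 SD if a 20-40 point imbalance goes unadjusted. At the low end this is negligible; at the high end it is about a third of the planned effect. If season were in fact screened, what remains is smaller. The T1-T2 interval is 6 months in both arms, so length of follow-up is not at issue. This is a worthwhile and inexpensive improvement, not a flaw that invalidates the design.

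**What to change.** 1. Include intake wave (fall 2018, spring 2019, fall 2019, spring 2020) as a prespecified fixed factor in every T2 and T3 model, independent of any balance test. For families without a club, use the wave in which their T1 falls.
2. Report T1 date and the sign-up-to-T1 interval by arm, so that readers can see whether timing differed.

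The cost is three degrees of freedom. Under the strongly unbalanced mix above, the SE also grows by about 5% and power falls from about 80% to about 76%; with a balanced mix the loss is close to nil. Both steps work for families already surveyed, provided that sign-up and survey dates were recorded. A new rule fixing T1 dates for no-club families is not requested, because Trial status has recruitment closing in March 2020.

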Other potential limitations relate to methodological as well as practical challenges. A practical challenge concerns the probability of attrition among participants allocated to the control group; if FCD is perceived as an attractive offer, being assigned to the wait-list with the prospect of being offered the intervention in six months might be difficult to accept. Because we are not able to apply strict random allocation comparability between the intervention group and control group cannot be guaranteed and conclusions about causality are expected to be tentative rather than definitive. On the other hand, the study is conducted in a naturalistic setting, which can be regarded as a strength to represent the setting in which FCD is applied.

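### Families are allocated before trial consent and baseline, and disclosure of the arm is not tied to return of either, so some club-area families may consent and answer T1 already knowing their arm

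*Protocol article*

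**What the plan says.** The Recruitment section of the protocol article gives a numbered sequence, introduced by "In most cases, the recruitment process is as follows". At step 1 the family applies and "gives consent for VIVE to contact the family", which is permission to be approached and not consent to the trial. Allocation follows: "3) The project coordinator allocates participants to intervention or wait-list control". Then: "4) The project coordinator sends contact information and allocation condition to VIVE". After the club start dates are passed on, the list ends: "6) VIVE sends the first questionnaire (including electronic consent to participate) by text-message and e-mail; and (6) The project coordinator informs participants about allocation". The section adds: "In some cases, families will sign up after the FCD has started".

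Other sections bear on the point:
- Outcomes: the questionnaires are web surveys, with reminders by text message and e-mail.
- Allocation: most controls are expected to have signed up where no club exists yet.
- Blinding: participants cannot be blinded.
- Statistical analysis: endpoints are analysed "according to an intention-to-treat (ITT) principle and handle missing data with multiple imputations". The arms are compared at baseline with t-tests, and baseline variables with p < 0.1 become covariates.
- Discussion: attrition among controls is foreseen because "being assigned to the wait-list with the prospect of being offered the intervention in six months might be difficult to accept".

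**The concern.** Trial consent and the baseline measurement are in one document, and that document goes out after the arm has been decided. The sequence orders disclosure after T1 is sent, but what matters is whether T1 has come back. A family that answers late, perhaps after a reminder, may already have heard from the coordinator.

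Two things could then go wrong.

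1. **Consent may depend on the arm.** The Discussion recognises that a wait-list place may be unwelcome, but speaks of attrition. The same reaction can act at entry: a disappointed family does not open T1. It then has no consent and no data. An intention-to-treat set can hold only consenters, and multiple imputation fills gaps among recorded participants, so neither brings that family back.
2. **Baseline answers may depend on the arm.** All T1 outcomes are self-reported. Relief or disappointment at the allocation would appear in the balance t-tests as a pre-existing difference, and the p < 0.1 rule could then adjust for it as if it were one.

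Either effect would come on top of the lack of randomisation that the article already admits.

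**Working it through.** **Sequence.** Contact permission (step 1) → allocation (3) → arm sent to VIVE (4) → T1 with trial consent sent (6) → arm disclosed (second 6). No step states that T1 has been returned.

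**The plan's own power.** Inputs from Power considerations and Statistical analysis: 80 controls, 120 FCD families, SMD 0.35, baseline–post correlation 0.50, two-sided 0.05.
- Residual SD after baseline adjustment = √(1 − 0.50²) = 0.866
- SE = 0.866 × √(1/80 + 1/120) = 0.125 SD
- Power = Φ(0.35/0.125 − 1.96) = Φ(0.84) = 0.80, as stated

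Without baseline adjustment the same inputs give 0.68. The stated power therefore relies on T1 as a covariate.

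**Illustration A: consent that depends on the arm.** The article gives no consent rates. Assume that 90% of FCD families and 60–75% of wait-list families consent, and that willingness to consent is a standard normal tendency correlated ρ = 0.2–0.4 with the baseline-adjusted outcome. With a share p retained, the mean tendency among those retained is φ(z)/p:
- p = 0.90: 0.195
- p = 0.75: 0.424
- p = 0.60: 0.644

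The difference between arms is 0.229 at 75% and 0.449 at 60%. Bias = ρ × 0.866 × difference. The analysed numbers stay at 80 and 120, so the SE stays at 0.125. Null rejection = Φ(−1.96 − b/SE) + Φ(−1.96 + b/SE). Power with the bias against FCD = Φ((0.35 − b)/SE − 1.96).

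| Wait-list consent | ρ | Bias (SD) | Share of 0.35 | Null rejection | Power, bias against FCD |
|---|---|---|---|---|---|
| 75% | 0.2 | 0.040 | 11% | 6.2% | 70% |
| 75% | 0.3 | 0.059 | 17% | 7.6% | 64% |
| 60% | 0.4 | 0.156 | 44% | 23.8% | 34% |

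**Illustration B: baseline answers that depend on the arm.** Assume that controls report T1 shifted by s SD because they know their arm, and that the shift does not persist to T2. Baseline adjustment then carries a bias of 0.50 × s. For s = 0.2 the bias is 0.10 SD and null rejection is 12.6%. The baseline SE is √(1/80 + 1/120) = 0.144, so a shift of 0.2 SD would meet the p < 0.1 rule with probability about 0.40. In those cases the rule itself brings the bias in.

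**How much a hold could remove.** Both illustrations apply the effect to all 80 controls. If, purely for illustration, half of the controls could be kept unaware until T1 is returned, the removable part of the central case is 0.059/2 ≈ 0.03 SD (null rejection 5.6%). The Allocation section, which expects most controls from areas without a club, implies fewer than half.

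**The case against.** The list already sends T1 first, and the second (6) is most naturally a misprint for (7). That is fair. A reader might infer from the shared number that families are told at the same moment as, or before, T1 goes out; the text does not support this. Nor does it support saying that every family that does not answer at once will know its arm. No interval between sending and disclosure is given, so the right word is may. The sequence also covers most cases only, and the schedule and flow-chart figures, which are not shown, might clarify the order.

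It can also be said that a hold before disclosure is operational detail an article may leave to the full protocol. This carries less weight, because the article sets out the sequence step by step and the weakness lies in the order as stated.

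The Discussion concedes that comparability cannot be guaranteed and that causal conclusions are tentative. That caveat concerns non-random allocation. It does not mention consent or baseline answers that depend on the arm, so it does not cover this mechanism.

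The strongest objection is reach. Controls from areas without a club probably know their status at sign-up, and a hold on disclosure does nothing for them. This stands in full and limits what the fix can achieve. It also stands that the consent rates and correlations are assumed, that recruitment was expected to finish in March 2020, and that the article nowhere says coordinators record notice dates.

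**Conclusion.** The point holds in a limited form. In the usual pathway families are allocated before trial consent and baseline, and disclosure is listed after T1 is sent without being tied to its return. For some club-area families, consent and baseline answers may therefore depend on the arm, and neither intention-to-treat nor multiple imputation can repair that.

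The size is not known from the article. Under the assumptions of Illustration A the bias is 0.040–0.156 SD, with a central case of 0.059 SD (7.6% null rejection, or 64% power if the bias is against FCD). A reader might take these as the bias present in the trial, or as the gain from a reordering. They are neither: they are illustrations, and upper bounds on what a hold can remove. The direction may be either way.

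A reader might also infer that allocation is final at step 3. The Allocation section later moves non-attenders, families unable to attend and families with a delayed start into the control group. That is a separate threat to intention-to-treat and does not cure this one.

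The change is worth making because it is specific and cheap, and because without consent rates by arm the selection cannot be seen.

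**What to change.** 1. Keep the listed order, renumber the second (6) as (7), and state that the coordinator discloses the arm only once VIVE confirms that T1 with consent has been returned, or at a fixed closing date before club start.
2. Report T1 consent rates by allocated arm, with all families on the coordinators' lists as denominator, separately for club-area and no-club-area families.
3. Where notice dates exist, compare them with the T1 return date and run a sensitivity analysis excluding families whose T1 came back after notice. If such dates were not kept, say so.
4. State plainly that controls from areas without a club cannot be kept unaware of their status.

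The cost is small: one condition on the timing of coordinator messages, and counts from lists that VIVE already receives at step 4. The downsides are shorter notice for families before club start, a smaller sample in the sensitivity analysis, and a hold that can apply only to families not yet enrolled. If recruitment has closed, items 2 to 4 are what remain.
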